**Table 5.1-1 Basic information about the study drugs**

| **Drug names** | **Specification** | **Storage conditions** | **Manufacturers** |
| --- | --- | --- | --- |
| TQB2450 injection | 100 mg/10 mL  300 mg/10 mL | Store, transport, protected from light, at 2-8°C | Chia-tai Tianqing Pharmaceutical Co., Ltd. |
| Anlotinib hydrochloride capsules | 12 mg/capsule  10 mg/capsule  8 mg/capsule | Sealed, protected from light, below 25°C | Chia-tai Tianqing Pharmaceutical Co., Ltd. |

The above drugs are produced by Chia-tai Tianqing Pharmaceutical Co., Ltd., and the production lot numbers and expiration dates of specific drugs are detailed in the drug test reports.

- 1. **Packaging of the study drugs**

The research drug package contains the name of the research drug, drug lot number, specifications, storage conditions, expiration date, name of the sponsor, and other information, and states “for clinical research use only”. The sample label is as follows, specific to the actual use shall prevail.

| **TQB2450-Ib-11** | |
| --- | --- |
| **(For clinical research use only)** | |
| Drug names: | TQB2450 injection |
| Specifications: | ×××mg/10ml |
| Usage and dosage: | ×× |
| Storage conditions: | Store, transport, protected from light, at 2-8°C |
| Production lot number: | ×× |
| Expiration date: | ×× |
|  | Provided by Chia-tai Tianqing Pharmaceutical Co., Ltd. |

| **Anlotinib** | |
| --- | --- |
| **(For clinical research use only)** | |
| Drug names: | Anlotinib hydrochloride capsules |
| Specifications: | Capsule ×× mg, 14 capsules per box, aluminum foam plate |
| Usage and dosage: | Oral on an empty stomach before breakfast, 1 capsules daily, oral once daily on days 1-14 |
| Storage conditions: | Sealed, protected from light, below 25°C |
| Production lot number: | ×× |
| Expiration date: | ×× |
|  | Provided by Chia-tai Tianqing Pharmaceutical Co., Ltd. |

**Table 5.2-1 The sample label of the research drug**

- 1. **Management of the study drugs**

The co-organizer will provide an adequate amount of study drugs to ensure the completion of the study. In accordance with Good Clinical Practice (GCP) requirements, the research drug will be kept in the exclusive custody of the drug administrator and stored under appropriate storage conditions. Study drugs are dispensed as prescribed or medical advice, and the last remaining research drug is collected. Complete records are required for the dispensing and recall of study drugs.

- - 1. **First drug distribution**

After the subjects meet the requirements for enrollment in this study, the investigator will formulate a prescription or medical advice based on the randomized results. The medication manager dispenses the study medication according to the prescription or medical advice.

- - 1. **Distribution and recall of study drugs during follow-up**

TQB2450: TQB2450 was distributed according to the prescription or medical advice, and the subjects were given medication according to the protocol. After the completion of medication, the unopened TQB2450 was recovered.

Anlotinib hydrochloride capsules: In the course of the study, according to the frequency of visits of the subjects, according to the cycle, the anlotinib hydrochloride capsules of the next stage were distributed to the subjects at the end of the cycle, and the unused drugs and remaining drug packages in this stage were recalled.

During the study, TQB2450 and anlotinib hydrochloride capsules were not dispensed to subjects if they were considered by the investigator to be unsuitable for continued medication, and unused medication and drug packages were recalled.

- - 1. **Disposal or destruction of leftover drugs**

The used or partially used drug containers, bottles, infusion bags, and syringes of TQB2450can be locally disposed of according to the usage guidelines and operating procedures established by the study center and local institutions. Unopened drugs should be handed over to the co-organizer for disposal or destruction after the trial.

For the anlotinib hydrochloride capsules that have been distributed to the subjects, the remaining drugs of the last time should be recalled. For the drugs that have not been distributed to the subjects, they should be handed over to the co-organizers for disposal or destruction after the end of the trial together with the remaining drugs recovered during the trial.

- 1. **TQB2450preparation method**

Aseptic principles should be strictly followed during the preparation process. Under aseptic conditions, extract the desired dose of TQB2450from the glass bottle and aseptically dilute it with sterile, non-heated physiological saline to a total volume of 250ml in an infusion bag. Gently invert the solution without shaking to ensure adequate mixing.

As an injectable medication, it should be visually inspection for the presence of particulate matter and discoloration before administration. The drug is a clear to slightly opalescent, colorless to pale yellow liquid. If the solution appears cloudy, discolored, or in the presence of visible particles, it should be discarded. Do not shake the vial.

TQB2450 does not contain preservatives and IV bags containing TQB2450 must be used immediately after dilution/mixing. If the TQB2450 dilution cannot be used immediately, the method of storage is as follows:

- The total storage time from opening the TQB2450 vial to the end of injection should not exceed 6 hours at room temperature;
- The total storage time should not exceed 24 hours in the refrigerator of 2 ℃-8 ℃ without freezing and shaking.
  1. **Administration regimens of the study drugs**
     1. **Administration principles**

During the study period, every 21 days will be one treatment cycle. More than 3 days per treatment cycle will be considered as reasonably delayed dosing, the subsequent administration time was calculated according to the actual date of the previous administration. No other anticancer therapy was allowed during the medication. Patients with the disease control (CR+PR+SD) and who can tolerate adverse effects continue the medication until disease progression or intolerance.

- TQB2450: On the first day of each cycle (D1), a fixed dose of 1200mg will be administered intravenously using an infusion set with a filter membrane, and infused for 60 ±10 minutes. The infusion time starts with the beginning of the TQB2450 infusion and ends with the completion of the TQB2450 infusion and normal saline flushing.
- Anlotinib hydrochloride capsules: According to the 3+3 dose climbing test, the maximum tolerated dose was determined as the initial dose. Before breakfast, take anlotinib orally on an empty stomach( TQB2450 was administered on an empty stomach within±5min of the start of infusion on day 1 of each cycle ),1 tablet per day. Continue the drug administration for 2 weeks and stop for 1 week. If there are missed medications and the interval from the next medication is <12 h, no medication is supplemented. If there was a vomiting event during the treatment, it was necessary to take the medicine if there were formed capsules in the vomit. If no capsule was formed, no supplement was given.
  - 1. **Infusion reaction processing**

Infusion-related reactions may occur with the administration of TQB2450. Symptoms may include fever, chills, rigors, sweating, and headache.

To prevent infusion reactions, H1 blockers (diphenhydramine 50mg IV, or equivalent) and acetaminophen (500 to 650mg oral or IV) can be administered 30-60min before each infusion of TQB2450. Systemic glucocorticoid therapy for the control of infusion reactions or immune-related adverse events had to be tapered for at least 2 weeks before the next dose of study drug at a dose that did not suppress immune-system function (prednisone or equivalent, ≤10mg per day).

Potential infusion-related reactions were observed during infusion of TQB2450 and 30min after completion of infusion.

Infusion rate regulation and/or treatment interruption/cessation for infusion-related reactions depends primarily on severity, as shown in the table:

**Table 5.5-1 Adjustment measures for infusion reaction**

| Grades of AEs  (NCI-CTCAE v5.0) | Adjustment measures |
| --- | --- |
| Grade 1- mild  It is not recommended to interrupt the infusion and clinical intervention for transient mild reactions | The rate of drop was reduced by 50% and any worsening symptoms were closely observed, and clinical intervention was performed if necessary. |
| Grade 2- moderate  Treatment or fluids should be suspended and systemic therapy (e.g., antihistamines, nsaids, anesthetics, intravenous fluids) should be given immediately. Prophylactic therapy is recommended for 24 hours or less. | Treatment with TQB2450 was suspended and resumed when the infusion reaction had resolved to grade 0-1 with a 50% reduction in the infusion rate. During this period, any worsening symptoms were closely observed and appropriate therapeutic interventions were initiated according to local medical practices. |
| Grade 3- severe  Symptoms persist, such as a slow response to systemic therapy and suspension of infusions, relapses after rapid resolution, and hospital admission due to complications. | Treatment with TQB2450 was immediately and permanently discontinued, and appropriate therapeutic interventions were implemented according to local practice. |
| Grade 4- life-threatening and requiring urgent medical intervention |  |

If the infusion rate of TQB2450 is reduced by 50% (90±10min) because of an infusion reaction, this reduction must be maintained for the next scheduled infusion. If an infusion reaction was not observed at the next scheduled infusion, the infusion rate could be returned to the baseline rate during subsequent infusions.

- - 1. **Adjustment of administration regimens**
       1. **General principles for adjustment of administration regimens**

When a toxic reaction occurs, the investigator may refer to the following rules for delay or dose adjustment. The reason for the delay or dose adjustment, the supportive therapy taken and the results should be documented in the subject's medical record and EDC.

If the investigator determines that the dosing adjustment differs from the proposed adjustment rule, after consultation and communication with the sponsor, the investigator will make the appropriate adjustment with reference to clinical practice guidelines or previous clinical experience, and the relevant reasons will be recorded in the subject’s medical record.

- Toxic reactions should be graded according to the NCI CTCAE 5.0;
- In case of simultaneous occurrence of severe toxicity of different severity levels, adjustments should be made according to the highest level observed;
- Treatment delays due to toxicity caused by anlotinib capsules could be delayed up to 35 days after the start of day 1 of the cycle (i.e., a 14-day delay in planned treatment) to allow adequate time for the subject to recover from any toxic effects caused by anlotinib hydrochloride. If a subject is unable to resume treatment by day 35 after the last dose, the subject must discontinue anlotinib hydrochloride treatment;
- Treatment delays due to toxic reactions caused by TQB2450 could be delayed up to 12 days after the start of day 1 of the treatment cycle;
- If subjects require permanent discontinuation due to toxic reactions (e.g., immune-related pneumonitis) of TQB2450, monotherapy with anlotinib should be continued until disease progression or unacceptable toxicity (whichever occurs first);
- If subjects require permanent discontinuation due to toxic reactions (hypertension, proteinuria, etc.) of anlotinib, monotherapy with TQB2450 should be continued until disease progression or unacceptable toxicity (whichever occurs first);
  - - 1. **Criteria for Dose Delay**

All of the following conditions should be met before starting treatment in any cycle, otherwise, a delay in administration is required:

- Absolute neutrophil count ≥1.5×109/L;
- Platelet count ≥75×10^9^/L;
- Hemoglobin（Hb）≥80g/L;
- Proteinuria ≤2+;
- Hand-foot skin reaction and hypertension ≤grade 2;
- Other toxicities until recovery to ≤grade 1

During the administration period (1-14 days) of anlotinib every cycle, if toxic reactions occur and the medication needs to be delayed, the maximum delay time should not exceed 5 days. If the medication cannot be continued for more than 5 days, the remaining anlotinib will not be administrated in this cycle.

- - - 1. **Dose modification**

Dose modifications for the TQB2450 were not allowed in principle throughout the study.

For anlotinib hydrochloride capsules, according to the 3+3 dose climbing test, the maximum tolerated dose was determined as the initial dose. If the initial dose is 12mg, dose level 1 is 10mg, and dose level 2 is 8mg; If the initial dose is 10mg, dose level 1 is 8mg; If the initial dose is 8mg, there was no down-dose selection. Any subject who required a reduction in the anlotinib capsule dose would continue to receive the reduced dose for subsequent cycles. Any subject who has undergone two dose reductions and requires a third reduction due to toxic reactions must discontinue the study treatment.

Principles of dose modifications related to anlotinib hydrochloride capsules.

- Hematologic toxicity

1. Thrombocytopenia

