Preventive medication is not recommended before administration. However, when the subject experienced infusion reactions of grade 2 or less and could resume medication after treatment, the investigator could use premedication to prevent the recurrence of infusion reactions. Antihistamines, antipyretic analgesics, and glucocorticoids at doses of 10mg or less per day could be used to prevent the recurrence of infusion reactions. Pretreatment could be administered on the basis of clinical experience at each site. Systemic corticosteroids needed to control infusion reactions or immune-related adverse events had to be tapered for at least 2 weeks, and the immunosuppressive dose (equivalent to ≤10 mg of prednisone per day) had to be discontinued by the time of the next dose of study drug. In subjects allergic to diagnostic imaging contrast, steroids may be administered as prophylactic therapy. Subjects who were already taking hormone replacement therapy before enrollment could continue hormone replacement therapy after enrollment.

Subjects could receive supportive care. Supportive care could be combined with the following medications or related treatments: antibiotics, analgesics, hormones, psychotherapy, and any other symptomatic treatment necessary to provide optimal supportive care. Other investigational antineoplastic drugs or antineoplastic chemotherapy/endocrine/immunotherapy were not included in the definition of supportive care.

All treatments that the investigator considers no effects on study endpoints may be administered, such as unconventional therapies (e.g., herbal or acupuncture) and vitamin/mineral supplements. Bisphosphonates are allowed for subjects with bone metastases during the trial.

Palliative radiation therapy in a small area (<5% bone marrow region) will be allowed for subjects with uncontrolled pain of bone metastases after systemic therapy or topical analgesia, the premise is that the radiation field does not include the target lesion.

During treatment, granulocyte colony-stimulating factor (G-CSF) and other hematopoietic growth factors could be administered if the clinical presentation suggested or the investigator judged that it was necessary to treat acute toxic effects such as febrile neutropenia. Subjects were allowed to use erythropoietin on a long-term basis.

1. Study procedures and assessments
   1. Study procedures
      1. Stage 1: 3+3 dose escalation trial

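### The 50% cut in TQB2450 infusion rate is given as 90±10 minutes, but half rate takes about 120; separately, section 5.6.2 calls prednisone ≤10 mg/day immunosuppressive, against the rest of the protocol

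*Protocol*

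**What the plan says.** **Infusion time.** Protocol section 5.5.1 gives a fixed 1200 mg of TQB2450 on day 1 of each cycle, "infused for 60 ±10 minutes". The timed period starts with the drug and "ends with the completion of the TQB2450 infusion and normal saline flushing". Section 5.4 dilutes the dose to 250 mL, and the dose modification section rules out TQB2450 dose changes in principle.

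Table 5.5-1 halves the rate after a grade 1 or grade 2 infusion reaction. The grade 1 row says "The rate of drop was reduced by 50" per cent. The grade 2 row stops the drug and resumes once the reaction has "resolved to grade 0-1 with a 50% reduction in the infusion rate". Neither row gives a time. The text below the table supplies one: "If the infusion rate of TQB2450 is reduced by 50% (90±10min) because of an infusion reaction", followed by "this reduction must be maintained for the next scheduled infusion". If that next infusion passes without a reaction, later ones may return to the base rate.

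**Steroid threshold.** Section 5.6.2 covers systemic steroids used for infusion reactions or immune-related events. By the next dose of study drug, it says, "the immunosuppressive dose (equivalent to ≤10 mg of prednisone per day) had to be discontinued". Earlier in the same paragraph, "glucocorticoids at doses of 10mg or less per day could be used to prevent the recurrence of infusion reactions". Section 5.5.2 covers the same steroids before the next dose and describes ≤10 mg/day of prednisone as not suppressing immune function. Exclusion criterion 25 (section 4.3) places immunosuppression above 10 mg/day.

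**The concern.** At a fixed dose and volume, infusion time is inversely proportional to rate. Halving the rate doubles the time, so 50% and 90 minutes cannot both hold from a 60-minute base. The figure of 90 equals 1.5 × 60, which suggests that a 50% longer infusion may have been written as a 50% lower rate.

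The conflict bites at the infusion after a grade 1 or 2 reaction. A site that works to the minutes re-exposes the patient faster than the 50% rule allows. A site that runs true half rate finishes outside the stated 80 to 100 minutes. From the nominal base, no site can meet both.

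The steroid sentence is a second, independent slip. Taken literally, it makes a site stop a steroid dose before re-treatment that section 5.5.2 accepts at that same point.

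**Working it through.** **Inputs**
- Base infusion time: 60 minutes, window 50 to 70 (section 5.5.1).
- Volume: 250 mL (section 5.4); dose fixed at 1200 mg (section 5.5.1).
- Rate cut: 50% for grade 1 and grade 2 (Table 5.5-1).
- Stated time for that cut: 90 minutes, window 80 to 100 (text under Table 5.5-1).
- Saline flush: counted in the infusion time, length not given (section 5.5.1).

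**1. Can the stated 90 minutes be reproduced from a 50% cut?** Time = volume / rate.
- Base rate: 250 / 60 = 4.17 mL/min. Half of that is 2.08 mL/min.
- Time at half rate: 250 / 2.08 = 120 minutes, the same as 2 × 60.
- Over the base window: 2 × 50 = 100 and 2 × 70 = 140 minutes.

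The figure is not reproduced. The half-rate range of 100 to 140 minutes meets the stated 80 to 100 at one point only, a 50-minute base slowed to exactly 100 minutes.

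**2. What cut do the stated minutes imply?** Cut = 1 − 60 / time.

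| Time (min) | Cut from the 60-minute base |
| --- | --- |
| 80 | 1 − 60/80 = 25% |
| 90 | 1 − 60/90 = 33% |
| 100 | 1 − 60/100 = 40% |

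Relative to true half rate, 90 minutes runs at (60/90) / 0.5 = 1.33, one third faster.

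**3. Could an unslowed flush explain it?** Let f be the flush minutes within the 60. Time at half rate is 2(60 − f) + f = 120 − f. The cut implied by 90 minutes is 1 − (60 − f)/(90 − f).

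| Assumed f (min) | Time at half rate (min) | Cut implied by 90 min |
| --- | --- | --- |
| 0 | 120 | 33.3% |
| 5 | 115 | 35.3% |
| 10 | 110 | 37.5% |
| 15 | 105 | 40.0% |
| 30 | 90 | 50.0% |

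Ninety minutes equals a 50% cut only if half of the base time is flush, which the protocol does not state.

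**4. Could a cut made partway through explain it?** If the rate is halved at minute t, the total is t + 2(60 − t) = 120 − t. At t = 30 this is 90 minutes, and 80 to 100 minutes corresponds to t between 40 and 20. The next scheduled infusion, however, runs at the reduced rate from the start, so t = 0 and the total is 120 minutes.

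**5. Steroid statements side by side** (prednisone or equivalent per day)

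| Place | How the dose is treated |
| --- | --- |
| Section 4.3, exclusion 25 | >10 mg is immunosuppressive |
| Section 5.5.2 | ≤10 mg is not immunosuppressive and is acceptable before the next dose |
| Section 5.6.2, premedication | 10 mg or less is allowed |
| Section 5.6.2, steroids before the next dose | ≤10 mg is immunosuppressive and must be stopped |

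The last row contradicts the other three.

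**The case against.** - **The minutes may describe the infusion during which the reaction occurred.** They sit in the conditional clause, and what carries forward is the reduction itself. A cut at minutes 20 to 40 would then give 80 to 100 minutes. This shows some ambiguity but does not rescue the text: earlier or later reactions fall outside the window, the grade 2 suspension adds time, and the only figure in minutes still cannot describe a full infusion at half rate.
- **The intended figure is not known.** Because 90 is 1.5 × 60, the error may lie in the 50% rather than in the minutes. This stands. Repeating 50% in two table rows favours that figure but does not prove it, and the choice is clinical.
- **In section 5.6.2 the slip may be a lost negation.** The sentence may have meant tapering to a non-immunosuppressive dose of ≤10 mg, in which case the inequality is right. This also stands, but the threshold comes out the same.
- **The consequences are modest.** The bedside instruction in Table 5.5-1 is clear, and grade 3 and 4 reactions end TQB2450 treatment. The next infusion is slower than base on either reading, premedication is available, and patients are watched during the infusion and for 30 minutes afterwards. A site would probably query the steroid sentence, because its own paragraph contradicts it. All of this limits the harm without making the instructions consistent.
- **The two points are unrelated.** They are, and each should be judged on its own. The steroid point involves no arithmetic.

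**Conclusion.** Both points hold.

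The stated 90±10 minutes does not correspond to a 50% rate cut from the 60-minute base. Half rate takes about 120 minutes: 100 to 140 over the permitted base window, or 105 to 120 from the nominal base if up to 15 minutes of unslowed flush is assumed. This rests on the fixed dose and volume and on the reduced rate applying to the whole of the next infusion.

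The steroid sentence in section 5.6.2 conflicts with section 5.5.2, with exclusion criterion 25 and with the premedication allowance in its own paragraph. Whether the slip is the inequality or a missing negation, the protocol's threshold for immunosuppression is above 10 mg/day.

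These are faults in point-of-care safety rules and should be corrected. They do not touch sample size, power or the PFS conclusion.

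**What to change.** 1. **Text under Table 5.5-1.** If the 50% cut is intended, change the time to about 120 minutes, for example 120±10 minutes. This leaves the table as it is. If 90 minutes is intended, change 50% to one third in the text and in both the grade 1 and grade 2 rows. The sponsor should confirm which is meant.
2. **Section 5.6.2.** Change the dose that must be stopped before the next study drug to >10 mg/day of prednisone or equivalent. Alternatively, restate the rule as in section 5.5.2, as a taper to a non-immunosuppressive dose of ≤10 mg/day. Both use the threshold already in the protocol, so no new clinical decision is needed.

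The cost is a wording amendment, with no change to the design or the sample size.

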**Table 5.5-3 Dose adjustments related to anlotinib hydrochloride capsules-** **the neutrophil count decreased**

| Grade of AEs | Recommended actions | Adjustment of administration regimens |
| --- | --- | --- |
| Grade 1 | Planned visits | Maintain the original dose |
| Grade 2 | Delayed dosing until recovery to ≤grade 1 | Maintain the original dose |
| Grade 3-4 | Delayed dosing and medical intervention treatment until recovery to ≤grade 1 | reduce 1 dose level |

- Nonhematologic toxicity

1. Abnormal liver function (elevated ALT, AST, or TBIL)

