**Table 5.5-6 Dose adjustments related to anlotinib hydrochloride capsules-bleeding events**

| Grade of AEs | Recommended actions | Adjustment of administration regimens |
| --- | --- | --- |
| Grade 1 | Planned visits | Maintain the original dose |
| Grade 2 | Delayed dosing until recovery to ≤ grade 1 | reduce 1 dose level, if it recurs, permanent termination of treatment is considered |
| ≥Grade 3 | Permanent termination of treatment | / |

1. Hypertension

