**(4) Grading the severity of AEs**

Grading the severity of AEs are assessed by the NCI-CTCAE version 5.0.

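### The rule that simultaneous severe toxicities follow the highest grade can, read literally, select a milder action than one of the toxicities calls for by itself

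*Protocol*

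**What the plan says.** Section 5.5.3.1 of the protocol grades toxic reactions by CTCAE 5.0 and then gives the rule for concurrent events: "In case of simultaneous occurrence of severe toxicity of different severity levels, adjustments should be made according to the highest level observed". The safety section repeats the grading standard: "Grading the severity of AEs are assessed by the NCI-CTCAE version 5.0".

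The anlotinib actions stand in Tables 5.5-2 to 5.5-9. For bleeding, Table 5.5-6 states "≥Grade 3 | Permanent termination of treatment". For a grade 2 bleed it delays dosing and adds "reduce 1 dose level, if it recurs, permanent termination of treatment is considered". For neutropenia, Table 5.5-3 states "Grade 3-4 | Delayed dosing and medical intervention treatment until recovery to ≤grade 1 | reduce 1 dose level", and Table 5.5-4 has the same row for abnormal liver function. Table 5.5-8 also delays and reduces by one level for grade 3-4 hand-foot skin reaction.

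The dose steps are in the section on dose modification: "If the initial dose is 12mg, dose level 1 is 10mg, and dose level 2 is 8mg". It adds: "Any subject who has undergone two dose reductions and requires a third reduction due to toxic reactions must discontinue the study treatment".

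For TQB2450, Table 5.5-10 lists actions by type and grade of immune-related reaction. Some rows suspend treatment and others discontinue it.

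**The concern.** A rule that selects by grade protects the patient only where the action becomes stricter, or at least no milder, as the grade rises, and where this holds across toxicities as well as within one table. Here the threshold for stopping differs by toxicity. Bleeding stops anlotinib at grade 3, while neutropenia and liver abnormality do not stop it even at grade 4. When such events coincide, the literal rule lets the second, higher-graded event displace the stopping row. The sicker patient then gets the milder instruction, and a drug that the bleeding row would have ended could be restarted. What is at stake is the clarity of a safety instruction, not the analysis.

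**Working it through.** No calculation applies; the check sets the rows side by side.

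**Step 1: what 'level' means.** The bullet directly before the rule fixes CTCAE 5.0 as the grading system, so the highest level is the highest CTCAE grade. How restrictive the action is does not enter the selection.

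**Step 2: anlotinib.** Bleeding is the only toxicity whose grade 3 row ends the drug. The grade 4 actions for the other toxicities are:

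| Toxicity at grade 4 | Table | Action | Milder than the grade 3 bleeding row? |
|---|---|---|---|
| Platelets | 5.5-2 | Terminate | No |
| Neutrophils | 5.5-3 | Delay, one level down | Yes |
| Liver function | 5.5-4 | Delay, one level down | Yes |
| Hypertension | 5.5-7 | Terminate | No |
| Hand-foot skin reaction | 5.5-8 | Delay, one level down | Formally yes |
| Other nonhematologic | 5.5-9 | Terminate | No |

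Proteinuria (Table 5.5-5) has no grade 4 row. Hand-foot reaction is marked formally because the section on common anlotinib AEs (6.5.6.2) describes it only up to grade 3, although Table 5.5-8 has a grade 3-4 row.

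**Step 3: consequence for dose.** Take grade 3 bleeding with grade 4 neutropenia. The bleeding row alone ends anlotinib. The literal rule selects the neutropenia row, which allows a restart after recovery one level lower: 12 mg to 10 mg, or 10 mg to 8 mg. A patient already reduced twice, from 12 mg to 8 mg, would need a third reduction and must stop, so the conflict disappears there. Where it remains, the result is the same one-level reduction that Table 5.5-6 gives for a first grade 2 bleed.

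**Step 4: TQB2450.** Table 5.5-10 shows the same pattern. Myasthenia gravis of any grade means discontinuation, while grade 3 colitis means suspension. If the myasthenia is grade 1 or 2, the higher grade belongs to the colitis and the literal rule selects suspension. The rule speaks of severe toxicity, and one could argue that low-grade myasthenia falls outside it. An example within grades 3 and 4 avoids that question: interstitial pneumonia of grade 3 means discontinuation, while adrenal insufficiency of grade 2 or higher, hence also grade 4, means suspension.

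**Step 5: is there an overriding sentence?** None of these sections says that a termination row prevails or that the most restrictive action applies.

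**The case against.** The strongest reply is that the rule ranks adjustments only, and termination is not an adjustment. Section 5.5.3.1 introduces its bullets as rules for delay or dose adjustment. In the anlotinib tables, termination stands under recommended actions with a slash in the adjustment column, and separate bullets cover what follows permanent discontinuation of either drug. This reading is possible but not compelling. The termination rows sit in tables titled as dose adjustments, under a heading on adjusting the regimen. Table 5.5-1 also lists "Treatment with TQB2450 was immediately and permanently discontinued" among its adjustment measures, although that table concerns infusion reactions to the other drug.

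A second reply is that the bleeding row is unconditional, and that the rule was surely meant to prevent under-reaction. That is very likely the intention, and most investigators would stop the drug. The wording still does not say so.

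Third, there are safeguards, and they do limit the effect:
- The rules are advisory, and the investigator may depart from them after consulting the sponsor and recording the reason. On the literal reading, however, stopping anlotinib is the departure.
- A new cycle requires an ANC of at least 1.5×10^9/L and most other toxicities back at grade 1 or lower, and anlotinib must resume by day 35 or stop. These conditions delay a restart but do not exclude one after a bleed has resolved.
- The Synopsis termination criteria use mandatory wording for intolerable reactions or severe events that the investigator confirms. They cannot cover every severe event, because the delay-and-reduce rows for grades 3 and 4 would then have no use. The matter returns to the investigator's judgment, as the section on investigator withdrawal decisions also puts it.

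Table 5.5-10 does not remove the anlotinib conflict for liver events. It concerns immune-related reactions, and section 5.5.3.1 continues anlotinib alone when TQB2450 is stopped for toxicity.

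**Conclusion.** The sentence is wrong as written, because a higher CTCAE grade does not always carry the stricter action. For anlotinib the clear cases are grade 3 bleeding with grade 4 neutropenia or grade 4 liver abnormality, and formally with grade 4 hand-foot skin reaction. Comparable cases exist for TQB2450. The conclusion rests on taking level as CTCAE grade and on reading adjustment to include termination.

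The priority is low. A reader might infer that the protocol obliges investigators to re-dose after a grade 3 bleed. It does not, since the rules are advisory and the investigator can end treatment. A reader might also take the share of conflicting table rows as a measure of risk. The protocol gives no co-occurrence rates, so no frequency can be stated. Nor does anything here bear on PFS or any other endpoint.

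**What to change.** Replace the sentence in section 5.5.3.1 with: *When toxicities occur together, apply for each drug the most restrictive action indicated by any of them; a row indicating permanent termination or discontinuation always prevails.* This settles the anlotinib tables and Table 5.5-10 together, and also the case of two toxicities of equal grade, on which the present wording is silent. The cost is one sentence in a protocol amendment. It adds no patients, visits or data.
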